The comprehensive evaluation is being conducted in those 42 health facilities implementing GHI with matched control health facilities. Matching of intervention and control facilities was done based on pre-determined variables such as the level of care (primary, secondary, or tertiary), volume of outpatient visits, bed capacity and availability of human resources (number of physicians, nurses, and other allied healthcare professionals). The data on the facility level characteristics was obtained from the GHS and the Christian Health Association of Ghana (CHAG) Secretariat (the largest faith-based health service provider in Ghana) and we considered a large pool of potential ‘control’ health facilities from the Central Region and Western Region (Fig. 1). The advantage of using a quasi-experimental design with matched control facilities ensures that all the exposure variables stay the same across the intervention and control facilities except for the intervention arm, i.e., GHI-related activities.

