### Study intervention

The first phase of the GHI, a three-year (2018–2020) programme funded by Bayer AG and implemented through the GIZ, was designed to improve risk assessment and management of hypertension and CVD in public health facilities and hospitals in the GAR. Its primary objective was to improve prevention, detection or diagnosis, and management of CVD. The GHI includes five main components: (i) Stakeholder engagement and development of national guidelines for the management of CVD, (available in hard copies and a digital app); (ii) Training of healthcare workers coupled with coaching / mentorship visits; (iii) Equipment supplies for the diagnosis and treatment of CVD; (iv) Training of healthcare workers for the collection of facility-level data for programme monitoring and the GHI programme team worked with the Policy, Planning, Monitoring and Evaluation Division of the GHS to include important NCD indicators including CVD in the District Health Information Management System (DHIMS2) to facilitate facility-level routine data collection and reporting; and (v) Establishment of a round the clock (“24/7”) CVD support center.

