### Statistical analysis

Quantitative data is analyzed by descriptive statistics for demographic, socio-economic and other patient-, provider- and health system level factors between the intervention and control facilities. Differences in service delivery indicators, process of care measures (prescription of guideline directed medical therapy) and clinical outcomes (BP control) will be compared between the intervention and control facilities. The chi-square test is used to evaluate differences between categorical variables. Two-sided p-values < 0.05 will be considered statistically significant. Composite performance scores are defined by determining the proportion of patients who receive concordant care compared to patients who receive discordant care between the intervention and control facilities. Linear and logistic regression analysis techniques are used to assess determinants of health outcomes, processes of care measures, and treatment satisfaction [33]. Random-effects regression analyses will be used to account for cluster effects and imbalances between intervention and control group health facilities; Effect sizes will be presented as risk ratios for binary outcomes, and as mean differences for continuous outcomes; 95% confidence intervals (CI) will be given for both. Missing data in outcome measures will be handled by appropriate imputation methods.

A propensity score will also be created using logistic regression and will contain those variables associated with treatment at a health facility [34]. Analysis of clinical outcomes analysis will also use ANCOVA (analysis of covariance) to compare the prescription of evidence-based medicines, and mean change in BP and lipids between the intervention and control arm facilities [29]. Other outcome measures such as behavioural and biochemical risk factors will be analyzed using logistic or conditional logistic regression to adjust the comparisons for other variables. We shall also compare the percentages achieving clinical and behavioural targets between the intervention and control arm facilities.

The fidelity analysis will uncover the extent to which the GHI was fully or partially implemented by various health system stakeholders.

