Next, when analyzing the KAP survey we will report the demographic characteristics of healthcare providers by the intervention and control arm facilities, reporting the mean (standard deviations, SD) or median (25th and 75th percentiles) for continuous variables and frequencies (percentages) for categorical variables. Knowledge about CVD symptoms and modifiable risk factors will be reported as number (percent) by overall and intervention and control arm facilities. Next, each correct response for knowledge related questions will be assigned a score of 1 and the total score for the knowledge of CVD risk factors and treatment recommendations will divided by tertiles and classified as minimal, moderate, and high knowledge. The mean (SD) for knowledge of CVD risk factors and treatment will also be reported by intervention and control facilities. Finally, the correct scores for the knowledge of CVD risk factors and treatment strategies will be classified into high knowledge (> 75% correct responses) and poor knowledge (≤ 75% correct responses) using arbitrary threshold for comparison and also informed by the published literature [35] [36]. The chi-square test will be performed to investigate the difference in knowledge scores between intervention and control arm facilities across age-group, sex, and education strata. Bivariable and multivariable regression analyses will be performed to assess the factors associated with high knowledge of CVD symptoms, and modifiable risk factors. The unadjusted and adjusted odds ratio with 95% confidence intervals (CI) will be reported. The model will be adjusted for age, sex, type of health facility and type of healthcare worker.

Lastly, an interrupted time-series analyses (ITSA) is carried out to establish effects of the GHI on the screening, diagnosis, and management of hypertension / CVD, if aggregate facility-level monthly data are available from the DHIMS2. ITSAs apply segmented regression to assess the impact of events that have occurred at a clearly defined point in time. Data points recorded in the GHI enabled DHIMS2 system will be analyzed by month to examine trends over time and seasonality. We will also evaluate change in patient outcomes over time (e.g., mean systolic BP change).

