The study has several limitations. As health facilities are not randomly assigned to the intervention and control arms, it is possible that the arms will be imbalanced about important patient characteristics (age, disease patterns, severity), provider characteristics (education, professional training or practicing experience), facility characteristics (primary, secondary and tertiary) and ownership (public, quasi-government and faith-based). These would be addressed in analyses adjusted for any important patient or provider-level characteristics. Mixed methods (quantitative and qualitative assessments) data evaluation will complement the overall data triangulation and analytical approach. Another potential limitation of the evaluation process may be recall bias when obtaining interview data after the pilot implementation phase of the intervention, as adherence may vary.

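### Imbalance in facility level and ownership is assigned to patient- or provider-level adjustment and to random effects, and neither removes a facility-level difference between arms

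*Protocol article*

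**What the plan says.** The limitations paragraph under Evaluation Design Strengths and Weaknesses notes that facilities were not randomised. It lists possible imbalance in patient characteristics, provider characteristics, and then "facility characteristics (primary, secondary and tertiary) and ownership (public, quasi-government and faith-based". The next sentence gives the remedy for the whole list: "These would be addressed in analyses adjusted for any important patient or provider-level characteristics".

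The Statistical analysis section gives a second remedy: "Random-effects regression analyses will be used to account for cluster effects and imbalances between intervention and control group health facilities". It adds: "A propensity score will also be created using logistic regression and will contain those variables associated with treatment at a health facility". It does not list the variables in that score or say how the score will be used.

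Four other places bear on the point:

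- **Study Setting** describes the design-stage control: "Matching of intervention and control facilities was done based on pre-determined variables such as the level of care", together with outpatient volume, bed capacity and staffing. It then claims that the matched design keeps every exposure variable equal across arms apart from the intervention.
- **Statistical analysis**, on the provider knowledge survey: "The model will be adjusted for age, sex, type of health facility and type of healthcare worker".
- **Conceptual framework** expresses a hope, not a commitment, to run a difference-in-difference analysis for some effectiveness indicators.
- **Quantitative study component** plans a record review before and after the Ghana Heart Initiative (GHI) in both arms.

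**The concern.** Exposure was fixed by facility and by region: 42 facilities in Greater Accra against 56 in the Central and Western Regions. Facility attributes are therefore leading candidates for confounding. The limitations paragraph names two of them and then prescribes adjustment at the wrong level. The analysis section treats a random-effects model as if it dealt with both clustering and imbalance.

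If these sentences are followed as written, the standard errors would reflect clustering while the point estimate could still carry a difference in level or ownership. Such intervals look properly corrected but may be centred on the wrong value. The affected outcomes include prescribing and blood pressure control, which are primary and may plausibly vary with the kind of facility. The results are meant to inform national scale-up.

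**Working it through.** The plan states no figure on this point, so there is none to reproduce. The check has three parts.

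**1. Which protections reach which facility attribute**

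| Protection | Level of care | Ownership |
|---|---|---|
| Matching (Study Setting) | Named | Not in the list, which is introduced as examples |
| Limitations remedy | Not covered | Not covered |
| Random-effects regression | No covariate named | No covariate named |
| Propensity score | Possible; variables not listed | Possible; variables not listed |
| Provider-knowledge model | Facility type named | Not named separately |
| Difference-in-difference, if done | Removes time-fixed differences | Removes time-fixed differences |

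The knowledge model is introduced as one for factors associated with high knowledge, and the text does not say whether arm is among its terms. A difference-in-difference needs a pre-GHI round. The record review has one; none is described for the patient exit survey or the provider survey. The counts of 42 and 56 (ratio 56/42 = 1.33) rule out simple 1:1 matching, and no use of matched sets is described for the main outcome models.

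**2. What a random intercept does**

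Let the outcome of patient i in facility j be

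y = a + b·arm(j) + g·x(j) + d·z(ij) + u(j) + e(ij),

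where x is a facility attribute, z a patient covariate and u the facility random intercept. The intercept u is assumed to have mean zero and to be independent of arm. If x is left out and unrelated to z, the arm estimate is centred on about b + g × (mean of x in intervention facilities − mean of x in control facilities). The random intercept does not change this term.

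A simulation confirmed it. Only the 42 and 56 come from the document. The rest is assumed: 12 patients per facility, true arm effect 0, g = 5 units, random-intercept SD 3, residual SD 18, 25 replicates per setting. The expected bias uses whole facilities, for example 5 × (29/42 − 22/56) = 1.49.

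| Share with attribute, intervention v control | Expected bias | Estimate without x | Estimate with x as fixed effect | Difference |
|---|---|---|---|---|
| 50% v 50% | 0 | 0.39 | 0.39 | 0.00 |
| 60% v 40% | 1.01 | 0.84 | −0.15 | 0.99 |
| 70% v 40% | 1.49 | 1.50 | −0.10 | 1.60 |
| 70% v 30% | 1.93 | 2.34 | 0.46 | 1.87 |

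The Monte Carlo standard error of each estimate is about 0.21 to 0.28, so single entries are noisy (0.39 appears where the bias is zero). Both models were fitted to the same data sets, so the last column is the cleaner comparison, and it tracks the expected bias closely. A random intercept plus patient adjustment leaves essentially all of the bias; the fixed facility covariate removes it within simulation error.

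**3. Possible size here**

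Bias = imbalance × effect of the attribute. The document gives neither level nor ownership by arm, so both inputs are assumed:

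- 0.05 × 20 points = 1 point
- 0.15 × 20 points = 3 points

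The Sample size section targets a 10% relative difference and gives no control rate. At an assumed control rate of 50% the target is 5 points, and the bias would be 1/5 to 3/5 of it (20% to 60%). At an assumed 80% the target is 8 points, and the bias would be 1/8 to 3/8 (about 13% to 38%). The direction is unknown.

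**The case against.** The plan has more protection than the two faulty sentences suggest. Level of care is the first-named matching variable, the propensity score could hold facility variables, facility type is in the knowledge model, and a difference-in-difference would remove time-fixed facility differences. A random-effects regression can also carry fixed covariates, so the sentence need not mean that the random intercept alone removes imbalance. Conditional logistic regression is planned for some other outcomes and could use matched sets. A full covariate list is ordinarily left to the analysis plan, which is not shown.

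Much of this stands, and it limits the point. A reader might infer that level of care and ownership remain confounded with arm in every comparison. The document does not support that: level was matched on, the article calls imbalance only possible, and a propensity score is planned. A reader might also infer that controls are more often faith-based, because the GHI was designed for use "in public health facilities and hospitals in the GAR" while facility data came partly from a faith-based provider network. No ownership distribution by arm is given, so that is conjecture.

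The objection does not rescue the two sentences. The limitations remedy is stated, and it is stated at the wrong level; this is not a matter of omitted detail. Even read generously, the random-effects sentence names no covariate that would do the work. The conditional logistic analyses are described for behavioural and biochemical risk factors, not for prescribing or blood pressure control.

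**Conclusion.** The concern holds in limited form. The article assigns admitted facility-level imbalance to two methods that, as written, do not remove it. The gap is clearest for ownership, which is conceded as a possible imbalance but is in no listed matching variable or covariate set. For level of care the risk is residual: it was matched on, but the limitations paragraph still concedes possible imbalance, and the main comparisons name no facility-level covariate. That concession also conflicts with the Study Setting claim that matching keeps all exposure variables the same.

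The size of any bias is unknown. The 1 to 3 points above rest wholly on assumed inputs, and the bias would be zero if the arms happened to be balanced. The mechanism needs only the standard assumption that the random intercept is independent of arm.

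**What to change.** - **Primary arm comparisons:** enter level of care, ownership, outpatient volume, bed capacity and staffing as fixed covariates in the random-effects models, or name them as propensity-score variables and state how the score is used.
- **Statistical analysis and limitations text:** reword so that random effects serve clustering and named covariates, including facility-level ones, serve imbalance.
- **Study Setting:** replace the claim that matching equalises all exposure variables with a statement that it aims to balance the listed ones, so that it agrees with the limitations paragraph.

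A facility's own pre-GHI outcome mean may be added where it is available but need not be required. If the 1,200 were the record-review total over both timepoints (an assumption), there would be about 1,200/(98 × 2) ≈ 6 records per facility per timepoint, a noisy covariate.

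The cost is small. Three levels of care and three ownership types use 2 + 2 parameters, volume and beds 1 each, and staffing 1 to 3, so 7 to 9 among 98 facilities. The matching variables are already held; ownership has to be recorded for each facility. No new patient data are needed.

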## Conclusions

Independent robust scientific evaluations of supply-side hypertension and CVD care delivery models in LMICs are rare. To date, little research has helped to understand implementation challenges and opportunities that are at the core of complex health system interventions. Moreover, the CVD burden is increasing rapidly in LMICs such as Ghana, and there exists a critical window of opportunity to integrate and deliver high quality systems of care and prevention strategies to ameliorate the CVD burden. In this article, we have presented a comprehensive protocol that aims to study the effectiveness, the fidelity, the implementation processes, the sustainability, the conditions that can influence scaling-up of a CVD care delivery model, the GHI, in a low-resource setting.

## Figures and Tables

**Figure 1 F1:**
[figure not shown]
Intervention and Control Regions to Evaluate the Ghana Heart Initiative CHPS = Community Health and Planning Services = Rural Primary Health Care Facilities

**Figure 2 F2:**
[figure not shown]
Theory of Change that Underpins the Evaluation of the Ghana Heart Initiative

**Figure 3 F3:**
[figure not shown]
Overview of the RE-AIM Evaluation Framework

**Figure 4 F4:**
[figure not shown]
Summary of the evaluation components, tools and outcomes measures *Fidelity and Acceptability were only assessed in the interventional health facilities. KAP = Knowledge, attitude and practice.

**Table 1 T1:** Health service delivery evaluation: domains, indicators, and tools.

Domains	Process Indicators	Outcome Indicators	Sustainability Indicators
Safety	No. and proportion of sites having access to guidelines, equipment; Type of out-patient and emergency services available by facilities.	Annual death rate for CVD; Incidence of CVD; Prevalence of hypertension; Prevalence of CVD	Workforce appropriate (workforce adequate in volume and distribution); Equipment adequate.
Tools	Health facility survey; Key informant Interviews	Health facility survey; DHIMS2 dataset	Health facility survey; Key informant Interviews
Timeliness	Annual hypertension screening coverage; CVD preventive and treatment services offered.	Total waiting time for physician consultations; Total in-person consultation time; Treatment received within 24 hours of CVD admission.	Workforce sustainability (staff retention per year, staff stability per year).
Tools	Health faclity survey	Health facility survey	Key informant interviews
Effectiveness	No. of HTN patients seen; No. of CHD patients seen; No. of stroke patients seen; No. of heart failure patients seen; No. of hospitalizations by CVD conditions; Average length of hospital stays (in days); No. of acute emergency transfers related to CVD; No. of referrals to higher facilities for CVD; No. of referrals to lower health facilities for CVD.	No. and proportion of patient diagnosed with hypertension; Number and proportion of patients diagnosed with CVD; Number and proportion of CVD patients prescribed evidence-based medicines; Number and proportion of patients with BP < 140/90; Number and proportion of patients with LDLc< 100 and < 70 in those with CVD; Number and proportion of patients who do not smoke.	Linkages - referral pathways (coordination of care across providers, specialist access); No of referrals per year; No of specialist consultations per year.
Tools	Health facility survey	Health facility survey; DHIMS2 dataset; Patient exit survey	Health faclity survey; Key informant interviews
Patient centered care	No. of follow-up appointments.	Treatment satisfaction; Proportion of patients in regular follow-up.	Infrastructure (IT-internet access, equipment access, staff availability or shortage)
Tools	Health facility survey	Health facility survey; Patient exit survey; In-depth interviews	Health facility survey; Key informant interviews
Efficiency and budget impact	Cost per service for: Outpatient Visit Emergency Visit Hospital Admission	Equity Proportion of patients receiving care by socio-demographic groups.	Governance and Leadership Description of governance structure and leadership.
Tools	Health facility survey; Patient exit survey	Health facility survey: Patient exit survey	Key informant interviews

* BP = Blood pressure; CHD = Coronary heart disease; OPD = Out-patient department; CVD = Cardiovascular disease; HTN = hypertension; LDLc = Low density lipoprotein cholesterol; HMIS = Health management information system.

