**Methods::**

This study adopts a mixed- and multi-methods design comparing the effects of the GHI in 42 intervention health facilities (i.e. primary, secondary and tertiary) in the Greater Accra Region versus 56 control health facilities in the Central and Western Regions. The evaluation design is guided by the RE-AIM framework underpinned by the WHO health systems building blocks framework, integrated by the Institute of Medicine’s six dimensions of health care quality: safe, effective, patient-centered, timely, effi cient, equitable. The assessment tools include: (i) a health facility survey, (ii) a healthcare provider survey assessing the knowledge, attitudes, and practices on hypertension and CVD management, (iii) a patient exit survey, (iv) an outpatient and in-patient medical record review and (v) qualitative interviews with patients and various health system stakeholders to understand the barriers and facilitators around the implementation of the GHI. In addition to primary data collection, the study also relies on secondary routine health system data, i.e., the District Health Information Management System to conduct an interrupted time series analysis using monthly counts for relevant hypertension and CVD specific indicators as outcomes. The primary outcome measures are performance of health service delivery indicators, input, process and outcome of care indicators (including screening of hypertension, newly diagnosed hypertension, prescription of guideline directed medical therapy, and satisfaction with service received and acceptability) between the intervention and control facilities. Lastly, an economic evaluation and budget impact analysis is planned to inform the nationwide scale-up of the GHI.

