## General objectives and research questions

Adopting an implementation science approach, our study aims to assess the reach, the effectiveness, the fidelity, the implementation process, the maintenance, and will provide scientific evidence for scaling-up the intervention nationwide. The study is envisioned to provide important insight into barriers and facilitators of scaling up a supply-side quality improvement CVD programme in Ghana. The specific research questions are:

Has the Ghana Heart Initiative reached the target population?Has the Ghana Heart Initiative produced the desired changes on quality of hypertension / CVD service delivery i.e., *safety, effectiveness, timeliness, equitable, and patient-centered care* and health outcomes?Has the Ghana Heart Initiative obtained support from key stakeholders?Has the Ghana Heart Initiative been delivered as planned (fidelity)?Are the implementation approach and health system changes produced by the Ghana Heart Initiative sustainable?

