For the provider KAP survey and exit survey, the field data collection team(s) visit a health facility and capture a random sample of healthcare providers and patients available on the day of the visit. This method relies on random sampling and the effi ciency of the field team. In essence this means maximizing the number of potential respondents to be interviewed on the day of the visit i.e. all eligible patients exiting the facility are interviewed, all eligible healthcare providers present and available at the facility are interviewed [28] [29]. The field work is carefully timed so that it coincides with the day of a hypertension / CVD clinic. Prespecified **eligibility criteria** is applied for health facilities and study participants (providers and patients) for the quantitative evaluation. The health facility assessment survey is carried out in all GHI intervention facilities, and matched control health facilities to specific characteristics (example, level of care, volume of patients attending the clinic, bed size, human resources available, etc.). The provider survey is recruiting providers (doctors, nurses, physician assistants, pharmacists) aged 18 years and above, both males and females; presently working in the facility at least from the last 3 months. Further, a licensed provider is defined as a physician or a nurse, pharmacist or physician assistant who is directly involved in providing CVD related services (counseling, health education, or consultation services or pharmacological therapy). The provider survey excludes those healthcare workers who have a managerial position and do not provide any patient care. Also, a physician, nurse or pharmacist who has worked in the facility for less than 3 months is excluded from the provider survey. The patient exit survey is carried out among those aged 18 years, both males and females, and having physician diagnosis of hypertension or other CVD conditions. The exclusion criteria include patients having diseases associated with frequent hospitalization (advanced cancer, end stage renal disease) bedridden or debilitating conditions. The MRR is performed for the patient folders for those aged 18 years and above, both males and females, and having physician diagnosis of hypertension or CVD conditions-Medical records from 2018 to 2022 are being reviewed. The medical records of pregnant women and those patients having diseases associated with frequent hospitalization (advanced cancer, end stage renal disease); bedridden or debilitating conditions are excluded for the MRR.

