
### Data collection Tools, Indicators, and Strategies

The quantitative evaluation component is critical to learning whether intervention improves outcomes among patients seeking care for hypertension and CVD in health care facilities. This component includes the following sets of quantitative tools, specifically:

**Facility based structured survey**, including analysis of facility registries & clinical records, to capture indicators of quality-of-service delivery (input, process, outcome).**Interviews with healthcare providers** to assess the knowledge, attitude, and practice regarding hypertension and CVD.**Exit interviews with the patient** to assess the client’s perception of the CVD consultation or examination, as well as his / her recollection of the instructions that he / she received about treatment or preventative behaviour.**Review of medical records** to capture indicators of quality-of-service delivery before and after GHI implementation.**Health management information systems** data with data being aggregated monthly at facility level for each of the CVD outcomes of interest.

The rationale for selecting service delivery, processes of care, clinical and quality of care indicators are based on the aspirations to achieving optimal health service performance and to guide the health care planning as a continuous quality improvement tool to drive health service improvement and better health outcomes [30] [31]. The outcome indicators are chosen from the recommendations of the national and international guidelines focused on CVD as well as to reflect how the facility or provider level determinants affect individual health behaviour and wellbeing (Table 1).

The exit survey draws questions from previous patient exit and household surveys and were further adapted to fit the Ghanaian context. Demographic and socioeconomic questions were based on the Ghana Census and Demographic and Health Survey. The exit interviews with the patient examines the respondent’s perception of the CVD consultation or examination, as well as his/her recollection of the instructions that he/she received about treatment or self-care behavior. The survey also captures how patients perceive the quality of specific aspects of the health facility and its providers. Patients are asked to rate 27 aspects of the facility visit on a five-point Likert scale with related Emoji’s.

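### As worded and with its listed tools, the Table 1 equity indicator describes the social mix of patients already in care, so it does not answer the equity part of research question 2

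*Protocol article*

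**What the plan says.** In the protocol article, General objectives and research questions, the second question asks whether GHI produced the desired changes in service quality. The dimensions it names include "timeliness, equitable, and patient-centered care".

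Table 1 gives Equity one outcome indicator: "Proportion of patients receiving care by socio-demographic groups". Its tools are the health facility survey and the patient exit survey. The medical record review and the routine DHIMS2 data are not listed for it.

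Under Quantitative study component, exit-survey patients are those "having physician diagnosis of hypertension or other CVD conditions", and on the visit day "all eligible patients exiting the facility are interviewed". That section describes a before-and-after design for the medical record review only.

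The abstract sets 42 intervention facilities in Greater Accra "versus 56 control health facilities in the Central and Western Regions". Under Study Setting, facilities were matched on level of care, outpatient volume, beds and staffing. The limitations concede that "it is possible that the arms will be imbalanced about important patient characteristics" and propose adjusted analyses.

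Socio-economic items are available in the exit survey: "Demographic and socioeconomic questions were based on the Ghana Census and Demographic and Health Survey".

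**The concern.** An equity effect of GHI means that a gap in care between social groups became smaller. The indicator, taken literally, counts who is in the waiting room. Three things are absent: a denominator of people in need in each group, a measurement before GHI, and a comparator drawn from the same population.

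Two errors then become possible. If Greater Accra differs socially from Central and Western Regions, the indicator differs between arms even when GHI did nothing. If GHI closes a prescribing gap among attenders without altering who attends, the indicator does not move. In either case the equity part of research question 2 would be answered from a quantity that does not measure it.

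**Working it through.** **Stated figure.** The article gives no rate, effect or power for equity, so there is nothing to reproduce. Only the sample size comes from the plan: 1,200 less 20% is 960 evaluable. The equal split (480 per arm) and all rates below are assumptions.

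**1. What the indicator contains.** Everyone in the exit survey is diagnosed and leaving a facility. The proportion receiving some care is therefore about 100% in every group, and what can vary is each group's share of attenders. The source with a catchment denominator (DHIMS2) and the source with two time points (the record review) are both assigned elsewhere.

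**2. Mix alone, no GHI effect.** Two-proportion test, two-sided 5%, shares centred on 50%. Example, 45% v 55%: null SE = √(2 × 0.25/480) = 0.0323; alternative SE = √(2 × 0.2475/480) = 0.0321; (0.10 − 1.96 × 0.0323)/0.0321 = 1.14, giving 87%. For design effect 1.5, use 480/1.5 = 320 per arm.

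| Regional difference in mix | Rejection rate | With design effect 1.5 |
|---|---|---|
| 3 points | 15% | 12% |
| 5 points | 34% | 24% |
| 8 points | 70% | 53% |
| 10 points | 87% | 72% |
| 15 points | 99.7% | 97% |

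**3. Same inequity in both regions, different populations.** Let π be the disadvantaged group's share of the catchment population, with access 30% for that group and 50% for others. Share of attenders = 0.3π / [0.3π + 0.5(1 − π)].
- π = 30%: 0.09/0.44 = 20.5%
- π = 40%: 0.12/0.42 = 28.6%
- π = 50%: 0.15/0.40 = 37.5%

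With π = 30% in the intervention region and 40% in the control region, the indicator differs by 8.1 points with no GHI effect (83% chance of p < 0.05 at 480 per arm, clustering ignored).

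**4. A real gain, different populations.** Suppose GHI equalises access at 50% for both groups, so that the intervention share equals π, while control stays at 30% v 50%. Intervention minus control:
- π 30% v 30%: 30.0 − 20.5 = +9.5 points
- π 30% v 40%: 30.0 − 28.6 = +1.4
- π 30% v 50%: 30.0 − 37.5 = −7.5

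The same true gain is visible, nearly invisible or reversed, depending on π.

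**5. A gain among attenders.** Control prescribing is 70% v 50%, GHI 70% v 70%, with equal mix in both arms. A mix test stays at 5%. The difference in gaps is 20 points. With 240 per cell, SE = √[(3 × 0.21 + 0.25)/240] = 0.0606, ratio 3.30, power 91% (77% at design effect 1.5). If the gap only halves (GHI 70% v 60%), SE = √(0.91/240) = 0.0616, ratio 1.62, power 37% (26%). If the group is 20% of patients (96 v 384 per arm), full-closure power is 74% (57%). These cross-sectional figures assume that the regions had equal gaps before GHI.

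**6. Adding period.** There are now eight cells, seven unchanged at 70% or 50% and the last at 70%. The sum of p(1 − p) is 5 × 0.21 + 3 × 0.25 = 1.80. If the 960 records cover both periods (120 per cell), SE = √(1.80/120) = 0.122 and full-closure power is about 37%. If there are 960 records per period (240 per cell), SE = 0.087 and power is about 64%. Clustering is ignored.

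**The case against.** The strongest reply is that the cell is short and can be read otherwise: the proportion who receive indicated care, reported within each group. The Statistical analysis section defines composite performance by concordant care, so that reading is reasonable and close to the fix below. This stands as a possibility, but the cell does not say it, and on that reading too the numerator and denominator need stating.

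A reader might infer that the plan will run a significance test on attender mix and reach a wrong equity conclusion. The documents do not support that. No such test is stated for this row; the between-arm comparison is inferred from the general plan. Socio-economic factors are also assigned to descriptive statistics, and equity is neither a primary nor a named secondary outcome. The rejection rates above therefore show how the indicator would behave if tested, and are not a forecast.

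The facility survey includes registries and clinical records, so it may hold more than attender mix. No need-based or before-after use of them for equity is described. Figures 3 and 4 are not shown and could add detail, but Table 1 states both indicator and tools.

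Confounding of arm with region affects every outcome here, and the article acknowledges imbalance. The equity row differs because the proposed remedy fails: the social group is itself the outcome, so adjusting for it removes what is being measured.

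**Conclusion.** The point holds for the indicator as worded and with the tools listed. It gives the social composition of patients already in care. A difference between Greater Accra and Central/Western can reflect regional mix, and a change in the care gap among attenders would not register. It does not answer the equity part of research question 2.

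It would go too far to say that the study cannot assess equity, since the record review and the exit survey hold data for a better contrast. The size depends wholly on assumed shares, access rates, prescribing gaps and an equal split. Under those inputs, a 5- to 10-point regional difference in mix gives 34% to 87% rejection with no GHI effect (24% to 72% at design effect 1.5), and a true gain can change sign. The consequence is confined to one named dimension of one research question and leaves the primary outcomes untouched.

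**What to change.** - Redefine the Table 1 equity indicator as the between-group gap in care received, using guideline-directed prescribing and BP control, and state numerator and denominator. If within-group care was always meant, say so.
- For groups recorded in the medical record review (at least age and sex), list that review as an equity tool. Fit arm × period × group in the planned random-effects model and report the difference in gaps with a 95% CI.
- For socio-economic groups found only in the exit survey, which has no described round before GHI, report the arm × group gap difference with a 95% CI as a cross-sectional association. State that pre-existing regional differences in the gap may explain it, and do not call it a GHI effect.
- Use waiting time only if it is recorded per patient in the exit survey; Table 1 assigns it to the health facility survey.
- Keep attender mix as a descriptive case-mix table.

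The cost is a changed table entry, one added tool and extra model terms, with no new data. Two limits remain. Precision is low: about 26–37% power for halving a 20-point gap cross-sectionally, lower for small groups and lower again once period is added, so these are estimates to report with intervals. And the gap concerns diagnosed patients in care, so equity of access to diagnosis stays unaddressed.
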